## Abstract

**Background:**

Secondary prevention after acute coronary syndrome (ACS) is essential to reduce morbidity and mortality, but related studies have been fairly small or performed as clinical trials with non-representative patient selection. Long-term follow-up data are also minimal. A nurse-led follow-up for risk factor improvement may be effective, but the evidence is limited.

**Objective:**

The aims of this study are to perform an adequately sized, nurse-led, long-term secondary preventive follow-up with inclusion of an unselected population of ACS patients. The focus will be on lipid and blood pressure control as well as tobacco use and physical activity.

**Methods:**

The study will consist of a randomized, controlled, long-term, population-based trial with two parallel groups. Patients will be included during the initial hospital stay. Important outcome variables are total cholesterol, low-density lipoprotein (LDL) cholesterol, and sitting systolic and diastolic blood pressure. Outcomes will be measured after 12, 24, and 36 months of follow-up. Trained nurses will manage the intervention group with the aim of achieving set treatment goals as soon as possible. The control group will receive usual care. At least 250 patients will be included in each group to reliably detect a difference in mean LDL of 0.5 mmol/L and in mean systolic blood pressure of 5 mmHg.

**Results:**

The study is ongoing and recruitment of participants will continue until December 31, 2014.

**Conclusions:**

This study will test the hypothesis that a nurse-led, long-term follow-up after an ACS with a focus on achieving treatment goals as soon as possible is an effective secondary preventive method. If proven effective, this method could be implemented in general practice at a low cost.

**Trial Registration:**

International Standard Randomized Controlled Trial Number (ISRCTN): 96595458; http://www.controlled-trials.com/ISRCTN96595458 (Archived by WebCite at http://www.webcitation.org/6RlyhYTYK).

## Introduction

### Background

Clinical trials have identified several treatments with proven secondary preventive efficacy after an acute coronary syndrome (ACS) [1]. Implementation of this knowledge, however, faces a number of obstacles and has been more difficult than anticipated [2] for a number of possible reasons. Among these, clinical trials typically include selected populations with lower age and less comorbidity compared with patients in routine clinical practice. In addition, trials generally are rigorously performed during a fairly short period of time, while the clinical environment is complex and difficult to control and the treatment perspective often spans many years. In secondary prevention these difficulties have led to failures in terms of treatment goals and consequently failure in risk reduction [3].

To simplify secondary preventive follow-up procedures while also retaining a high level of treatment adherence, different strategies of telephone support have been evaluated [4-6]. Despite rigorous protocols, ambitious patient information packages, and frequent patient support, the results in terms of reduction of risk factor levels have been modest [7,8]. To some extent, this outcome may be explained by improvements in general care against which intervention results are compared. However, the published secondary preventive trials using telephone support have several weaknesses, including a low proportion of included patients relative to the target population [5,6]. Other weaknesses are age limits, extensive protocols requiring an alert patient, recruitment from selective secondary prevention programs, and exclusion because of comorbidity. Furthermore, a rapid routine intended to allow for prescription changes for lipid and blood pressure control to achieve treatment goals as soon as possible has mostly not been used. Moreover, low-risk patients have been included with a 12-month mortality rate around 2% [7,8]. Thus, more research in this area is needed.

### Study Objective

To improve secondary prevention, we have designed a trial with several important components. First, all patients after an ACS will be considered for inclusion regardless of age, and this population-based design will include all residents in the county of Jämtland, Sweden. Second, a maximally simplified, nurse-based, telephone follow-up protocol will be used, which will minimize resources needed as well as patient exclusions and make the methodology easy to implement. Third, a routine for prompt medication adjustment will be used to reach set treatment goals as quickly as possible. Finally, a long-term follow-up is planned with risk factor evaluation after 12, 24, and 36 months.

### Hypothesis

We hypothesize that in ACS patients, this nurse-based, telephone follow-up will reduce risk factor levels more effectively than usual care.

## Methods

### Trial Design

This study is planned as a randomized, controlled trial with two parallel groups and an allocation ratio of 1:1.

### Ethical and Research Governance Approval

Ethics approval has been received from the Ethics Committee, Umea University (09-142M). This paper presents the design of the study according to CONSORT requirements [9].

### Participants

All patients living in the county of Jämtland, Sweden, who were hospitalized with a diagnosis of myocardial infarction or unstable angina will be assessed for inclusion. Östersund Hospital is the only hospital in the county, and all patients, those in terminal care excluded, with symptoms of a suspected ACS are referred for diagnostic evaluation. It is a rural catchment area with a population of approximately 125,000 inhabitants. A routine for identification of all patients in the hospital with a possible ACS has been established in previous studies, and during a 3-month test period, the study nurses identified all patients with a final ACS diagnosis. In the present study, an ACS was defined as myocardial infarction type 1 or unstable angina with electrocardiogram changes (ST depression or T wave changes) suggesting myocardial ischemia. All patients with the physical and mental capacity to communicate by telephone will be eligible, which means that those with deafness or dementia will be excluded. The other exclusion criteria are severe, often terminal, disease and participation in another ongoing trial.

### Interventions

All eligible patients will be informed about the study and asked to give written informed consent. They will receive standard information about ACS concerning pathophysiology and risk factors according to established clinical practice during their hospitalization. They will also be offered a follow-up visit to a cardiology nurse and an outpatient follow-up according to usual care.

A study nurse will contact patients randomized to the intervention group by phone 1 month after discharge. Before the call, a blood sample for lipids will be taken and a standardized blood pressure control performed. Blood pressure will be measured after 5 minutes in the sitting position and after 1 minute standing. A district nurse will perform the tests; for patients in the intervention group living close to the hospital, a study nurse will do the testing. Cardiac symptoms and self-reported adherence with medication will be recorded. During the call, the patient will be informed about the test results and whether a change in medication is necessary. Tobacco use, physical activity, and dietary habits will be discussed. Smoking cessation will be encouraged and supported. Physical activity of moderate intensity 30 minutes or more on most days of the week will be encouraged but also adjusted to the individual patient’s capacity. Dietary advice to reduce saturated fat and increase fruit and vegetable intake will be given. If the patient’s cholesterol or blood pressure values are above target, medication will be adjusted after contact from a study physician. Tests will be repeated within approximately 4 weeks, and further adjustments made if necessary until target values are reached or no further changes can be considered realistic. The same routine, with an Hb1C test added, will be applied after 12, 24, and 36 months. The patient’s motivation to follow instructions will be assessed.

The target values are systolic blood pressure <140/<90 mmHg, total cholesterol <4.5 mmol/L, and low-density lipoprotein (LDL) cholesterol <2.5 mmol/L (optionally <1.8 mmol/L in patients at very high risk, eg, who have diabetes) [10,11].

Patients randomized to the usual care group will also be contacted by phone 1 month following discharge after blood pressure and lipid profile measurements. Cardiac symptoms, self-reported compliance, tobacco use, and physical activity will be recorded. The treating physician, usually a general practitioner, will provide all medical care and receive the test results (lipid profile and blood pressure), and no additional intervention will be given as a result of participation in the study. The scheduled controls of blood pressure and lipids in the study will be additive to the usual follow-up performed by the general practitioner. The same routine, with an Hb1C test added, will be applied after 12, 24, and 36 months (Figure 1). Participation in the study will otherwise not affect the standard of care in the usual care group.

The number of visits to the patient’s treating physician as well as visits to a nurse will be recorded to develop a picture of the number of medical assessments in the control and intervention groups.

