### Outcomes

Outcomes will be measured after 12, 24, and 36 months of follow-up. Outcome variables are total cholesterol, LDL cholesterol, and sitting systolic and diastolic blood pressure as well as the proportion of patients achieving the set target for these variables. Standing systolic and diastolic blood pressure, smoking rates, the proportion of patients treated with different secondary preventive drugs, diabetes control by Hb1C, and change in body mass index (BMI) and physical activity will also be measured. The LDL value at 36 months will be analyzed as the primary outcome. Analyses of the secondary outcomes will be exploratory. Blood pressure measurements are standardized as described above, and LDL values are calculated from the serum concentrations of cholesterol and fasting triglycerides using the Friedewald formula. Smoking (yes/no) and physical activity (duration/week) are self reported. Deaths are available in the hospital records and will be recorded to detect any survival difference between groups.

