## Discussion

### Summary

Different approaches have been used to recruit patients for secondary prevention studies after an ACS. Some have involved contacting patients participating in rehabilitation programs [5], and others have identified patients with a previous diagnosis of coronary artery disease [6]. To avoid selection bias, a population-based approach is preferable and is the only way to obtain a reliable estimate of the proportion of excluded patients. Enrollment of the patients immediately after an acute event is probably the best way to achieve a high participation rate. This study covers all patients in a Swedish county, who will be eligible for inclusion after an ACS, thus avoiding selection bias. Thus, the study population will include even very old and very sick ACS patients, who are usually not part of randomized ACS studies. Their ability to participate in secondary prevention programs and their tolerability of medication when attempting to achieve set treatment goals are of great interest because these factors could have significant consequences for health economics and morbidity and mortality rates. The immediate recruitment and the logistics for including each and every ACS patient will show the true proportion of possible participants in the secondary preventive program.

A randomized design is necessary to reliably evaluate the effect of the intervention. Some investigators use a prospective cohort design, which makes it difficult to draw conclusions in terms of efficacy, particularly if the drop-out rate is high [12]. The design of the present study means that patients in the usual care group will be contacted by the study nurses to collect data about risk factors. This step adds a certain interference and possibly improvement in usual care but cannot be avoided if the results of the two groups are to be compared. The standard of care that is achieved in the intervention and control group can be assessed by comparing lipid and blood pressure values as well as other risk factor results with the corresponding values in other ACS populations.

We use an associated study physician for the intervention group to obtain immediate decisions about more qualified treatment changes. Based on the results of previous studies, rapid treatment decisions by someone directly involved in the study are related to more effective risk factor control [13].

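### As written, who takes the outcome blood pressure depends on arm among patients living near the hospital, which can bias the secondary blood pressure comparisons in either direction

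*Protocol article*

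**What the plan says.** All places are in the protocol article.

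- Interventions, default: "A district nurse will perform the tests".
- Interventions, exception: "for patients in the intervention group living close to the hospital, a study nurse will do the testing".
- Interventions, who delivers the intervention: "A study nurse will contact patients randomized to the intervention group by phone 1 month after discharge". The abstract adds that trained nurses manage this group toward set goals.
- Interventions, later visits: "The same routine, with an Hb1C test added, will be applied after 12, 24, and 36 months". These are the outcome times in the Outcomes section.
- Interventions, usual care: "Patients randomized to the usual care group will also be contacted by phone 1 month following discharge after blood pressure and lipid profile measurements". Neither the person measuring nor the setting is named.
- Discussion, Summary: "patients in the usual care group will be contacted by the study nurses to collect data about risk factors". The Interventions section describes this contact as a telephone call made after the measurements, so it does not show that study nurses take these blood pressures.
- Outcomes: "Outcome variables are total cholesterol, LDL cholesterol, and sitting systolic and diastolic blood pressure", together with the proportions at target. Standing blood pressure is measured too. LDL at 36 months is primary, and secondary outcomes are exploratory.
- Outcomes, safeguard: "Blood pressure measurements are standardized as described above". What is described is 5 minutes' rest sitting and 1 minute standing.
- Sample Size: a 5 mmHg systolic difference is one of the two effects on which the main calculation rests; the other is 0.5 mmol/L in LDL.

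**The concern.** A blood pressure reading depends partly on who takes it, through technique, rounding, the patient's familiarity with the nurse, and setting. If the observer is chosen the same way in both arms, these influences cancel on average. Here the choice is tied to allocation for part of the trial population. The exception covers nearby intervention patients only, and the nurses concerned deliver the intervention. That they know the allocation is not stated, but it follows from their role. They also work toward the <140/<90 mmHg goal, and a reading above it sets off medication review and repeat testing, so readings near the threshold are not neutral for them.

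Standardised rest and posture make readings more uniform but do not make the observer the same in both arms. The protocol describes neither a masked assessor nor an automated device. At stake is the interpretation of mean sitting and standing blood pressure and of the proportion at blood pressure target. A larger sample does not shrink a bias of this kind.

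**Working it through.** **1. The plan's own figure.** The Sample Size section states about 200 per group for a 5 mmHg systolic difference (two-sided alpha 0.05, power 80%) and gives no SD. Solving back:

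SD = 5 / [(1.960 + 0.842) x sqrt(2/200)] = 5 / 0.280 = about 17.8 mmHg.

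Forward, at SD 17.8 the normal-approximation formula gives 199 per group (161 at SD 16, 252 at SD 20). The figure is coherent with an SD near 17.8, but that SD is inferred here and not stated. Allowing an assumed 20% drop-out, 200 / 0.80 = 250, the planned number.

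**2. Bias from an arm-dependent observer.** Let f be the share of the intervention arm measured by study nurses, and d the mean of a study-nurse reading minus a district-nurse reading on the same patient. If all usual-care patients are measured by district nurses (an inference from the default):

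expected difference between arms = true effect + f x d.

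A negative d makes the intervention look better; a positive d hides benefit. The documents give neither f nor d. With assumed f of 30-70% and |d| of 0-5 mmHg:

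| f | \|d\| (mmHg) | \|bias\| (mmHg) | share of 5 mmHg |
|---|---|---|---|
| any | 0 | 0 | 0% |
| 0.3 | 2 | 0.6 | 12% |
| 0.3 | 3 | 0.9 | 18% |
| 0.5 | 2 | 1.0 | 20% |
| 0.5 | 5 | 2.5 | 50% |
| 0.7 | 5 | 3.5 | 70% |

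The last row multiplies two upper limits.

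**3. Effect on a systolic test when there is no true effect.** With SD 17.8 and 200 analysed per arm, SE = 17.8 x sqrt(2/200) = 1.78 mmHg. For a bias b, the two-sided rejection rate is Phi(b/SE - 1.96) + Phi(-b/SE - 1.96):

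- f 0.2, d 2 (b 0.4): 5.6%
- f 0.3, d 3 (b 0.9): 8.0%
- f 0.3, d 5 (b 1.5): 13.4%
- f 0.5, d 5 (b 2.5): 29%

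With small inputs the effect is negligible; with large ones it is not.

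**4. Can the analysis separate observer from arm?** The planned model (Statistical Methods) adjusts for sex and type of ACS, which say nothing about the observer. Under the stated rule, the indicator for a study-nurse reading is the product of arm and nearby residence. An observer term is therefore the same column as an arm-by-residence interaction. A model with arm, residence and observer can be fitted, but it treats any true difference in effect between near and far patients as observer error. In that model the arm effect comes from the patients living away from the hospital, the only ones measured by the same class of nurse in both arms.

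**5. Precision of that comparison.** Residence does not depend on allocation, so restricting by it preserves randomisation. If a share f lives nearby in each arm and the SD is unchanged, the SE grows by 1/sqrt(1 - f): 1.20 at f = 0.3, 1.41 at f = 0.5 and 1.83 at f = 0.7.

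**6. Proportion at target.** The same mechanism applies, but its size depends on how many patients lie close to 140/90. The documents do not give this, so no figure is offered.

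**The case against.** The strongest reply has four parts.

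- **Blood pressure is not the primary outcome.** LDL at 36 months is, and it is calculated from laboratory values; secondary analyses are labelled exploratory. This stands. A reader might infer that the trial's main conclusion is compromised; the Outcomes section does not support that. The 5 mmHg sample-size target gives blood pressure weight but no confirmatory role.
- **The usual-care measurer is not named.** This stands too. A reader might conclude that nearby controls are certainly measured by district nurses in another setting. The default sentence and the absence of a second exception make district nurses the likely reading, but the text does not state it. The flow chart was not available for this review and might settle it. If study nurses also test nearby controls, the observer is balanced and the error lies in the wording of the exception.
- **Size and direction are unknown.** Measurement is standardised, so an observer difference near zero is possible, and the bias could dilute the effect as well as inflate it. The documents do not support a claim that the blood pressure result will favour the intervention.
- **Adjustment can help.** It is tempting to say that no regression could remove the problem. That is too strong: a model with an observer term works if the treatment effect is the same near and far.

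What survives is that the stated rule ties the observer to the arm, and that the stated standardisation does not undo this.

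**Conclusion.** The point holds at moderate priority. On the text as it stands, the outcome blood pressure of nearby patients is taken under a rule that differs by arm, and in the intervention arm it is taken by staff who deliver the treatment. Sitting and standing blood pressure and the proportion at blood pressure target can be biased in either direction. For mean pressure the absolute size is 0-3.5 mmHg, resting wholly on assumed shares of 30-70%, assumed observer differences of 0-5 mmHg, and the inference that district nurses measure the usual-care arm. The primary LDL analysis is little affected, and no change in sample size follows. A reader might see a defect that must be cured before the trial can be interpreted; the exploratory status of these outcomes and the unknown size of any observer difference do not support that.

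**What to change.** 1. **One rule for both arms.** For the scheduled 12-, 24- and 36-month readings, let the measurer not depend on allocation, preferably district nurses for everyone. Interim checks can stay as they are. Having study nurses measure nearby patients of both arms would also balance the observer. It is second best, because it keeps observers who know the allocation and adds contact between controls and intervention staff; the Discussion already notes that study contact may improve usual care.
2. **Record the measurer** at each outcome reading, including readings already taken where this can be recovered.
3. **Sensitivity analysis.** Report the blood pressure outcomes in patients living away from the hospital, with the restriction defined by residence and applied alike in both arms. A result that differs from the full analysis may reflect either the observer or a different effect by residence, and should be read so.
4. **Clarify the text.** State who measures blood pressure in usual care. If study nurses in fact also test nearby usual-care patients, remove the restriction to the intervention group from the exception.

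**Cost:** existing staff, a scheduling change and a short protocol clarification. Nearby intervention patients lose a little convenience. Those already enrolled would change measurer during the trial. The restricted analysis is less precise, with an SE 1.20 to 1.83 times as large for nearby shares of 30-70%.

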**Figure 1 figure1:**
[figure not shown]
Study flow chart (BP=blood pressure).

### Outcomes

Outcomes will be measured after 12, 24, and 36 months of follow-up. Outcome variables are total cholesterol, LDL cholesterol, and sitting systolic and diastolic blood pressure as well as the proportion of patients achieving the set target for these variables. Standing systolic and diastolic blood pressure, smoking rates, the proportion of patients treated with different secondary preventive drugs, diabetes control by Hb1C, and change in body mass index (BMI) and physical activity will also be measured. The LDL value at 36 months will be analyzed as the primary outcome. Analyses of the secondary outcomes will be exploratory. Blood pressure measurements are standardized as described above, and LDL values are calculated from the serum concentrations of cholesterol and fasting triglycerides using the Friedewald formula. Smoking (yes/no) and physical activity (duration/week) are self reported. Deaths are available in the hospital records and will be recorded to detect any survival difference between groups.

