### Sample Size

A difference between groups in mean LDL of 0.5 mmol/L and in mean systolic blood pressure of 5 mmHg is considered clinically relevant and requires study groups of approximately 200 participants to be reliably detected (alpha .05, two-tailed, power 80%). Study groups of at least 250 participants are planned to allow for drop-outs. This sample size is also adequate for detection of clinically meaningful group differences in smoking rates (10%), proportion reaching treatment goals (10%), change in BMI (1.0), and change in physical activity (10%, proportion in a given activity level), calculated with two-tailed alpha .05, power 80%.

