### Statistical Methods

Mean values of blood pressure and lipid variables in the intervention and control groups will be compared using the *t* test for independent groups. Proportions will be compared using the chi-square test. The primary analysis will be performed according to the intention-to-treat principle using a linear regression model adjusting for sex and type of ACS. The adjustment is made to reflect the stratified randomization process. Per protocol analyses will also be performed. Secondary outcomes will be analyzed using the primary analysis model when continuous, and a logistic regression model, adjusting for the same covariates, when outcomes are binary. To assess indications of differential treatment effects across subgroups (ie, age, sex, comorbidity, level of education, and social classification), tests for interaction will be performed, although this aim is secondary because the study is not powered for this particular purpose. Adjustment for relevant baseline covariates will be performed in additional exploratory analyses of primary and secondary outcomes to evaluate the effect of possible baseline imbalance. All tests will be two-sided, and a *P* value of <.05 will be considered significant.

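### Smoking is analysed only as a whole-arm rate, which dilutes a cessation effect; a main analysis among patients smoking at the index admission would be more efficient

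*Protocol article*

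**What the plan says.** The Objective in the abstract names tobacco use as a focus, beside lipids, blood pressure and physical activity. Under Interventions the tobacco component is described as discussion of tobacco use in the calls, with "Smoking cessation will be encouraged and supported".

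Outcomes lists "smoking rates, the proportion of patients treated with different secondary preventive drugs, diabetes control by Hb1C" among the additional measures and defines the scale: "Smoking (yes/no) and physical activity (duration/week) are self reported". It names LDL at 36 months as primary and makes the analyses of secondary outcomes exploratory.

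Sample Size states: "This sample size is also adequate for detection of clinically meaningful group differences in smoking rates (10" (the bracketed figure is 10%). That figure and its companions are "calculated with two-tailed alpha .05, power 80" per cent. The size behind these claims is at least 250 per group planned; for LDL and systolic pressure the article says the target difference "requires study groups of approximately 200 participants to be reliably detected".

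Statistical Methods prescribes "a logistic regression model, adjusting for the same covariates, when outcomes are binary", the covariates being sex and type of ACS. Adjustment for relevant baseline covariates, none of them named, is foreseen in additional exploratory analyses. Participants sets no smoking criterion for eligibility, and nothing in the article restricts the smoking outcome to patients who smoked at inclusion.

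**The concern.** Support for stopping acts mainly on patients who smoke when they are admitted. In a whole-arm rate, those patients are averaged with never-smokers and long-standing ex-smokers, in whom little change is expected. The contrast shrinks in proportion to the share of smokers, while the noise does not shrink enough to compensate.

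The consequence is for interpretation of a named focus area. A worthwhile difference in stopping could appear as a whole-arm difference of a few points, well under the article's own 10-point benchmark, and be reported as no effect. The claim that the sample is adequate for 10 points may also give readers more confidence in a null smoking result than the design supports.

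**Working it through.** **Inputs from the article:** two-sided alpha .05; power 80%; 10% difference, read as percentage points; at least 250 per arm planned and about 200 needed, so 200 is used as the evaluable number; 1:1 allocation.

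**Assumptions (not in the article):** share of patients smoking at admission s = 15, 25 or 35%; among them 60% still smoke under usual care and 40% under the intervention; no relapse or uptake among the others.

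**Step 1: the article's own claim.** No control smoking rate is given, so the claim cannot be reproduced without assuming one. For rates a and b with mean p:

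n per arm = [1.96·√(2p(1−p)) + 0.84·√(a(1−a)+b(1−b))]² / (a−b)²

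| Control v intervention | n per arm for 80% power | Power at 200 per arm |
|---|---|---|
| 20% v 10% | 199 | 80% |
| 25% v 15% | 250 | 71% |
| 30% v 20% | 294 | 64% |

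So the claim holds at 200 evaluable per arm if the control rate is about 20% or lower, which means smoking in the intervention arm is at most half that under usual care. With all 250 evaluable it holds up to about 25%.

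**Step 2: what 10 points implies among smokers.** Arm difference = s × d, where d is the difference among baseline smokers, so d = 0.10/s:

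- s = 15%: 0.10/0.15 = 67 points
- s = 25%: 0.10/0.25 = 40 points
- s = 35%: 0.10/0.35 = 29 points

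**Step 3: power of the two analyses for d = 20 points.**

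Power = Φ{ [|a−b|·√n − 1.96·√(2p(1−p))] / √(a(1−a)+b(1−b)) }

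Worked for s = 25%, 200 per arm:

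- Whole arm: a = 0.25×0.60 = 0.15, b = 0.25×0.40 = 0.10, n = 200. (0.707 − 0.917)/0.466 = −0.45, power 33%.
- Admission smokers only: a = 0.60, b = 0.40, n = 200×0.25 = 50. (1.414 − 1.386)/0.693 = 0.04, power 52%.

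| s | Arm rates | Arm difference | Whole arm, n = 200 | Smokers only | Whole arm, n = 250 | Smokers only |
|---|---|---|---|---|---|---|
| 15% | 9% v 6% | 3 points | 21% | 34% | 25% | 41% |
| 25% | 15% v 10% | 5 points | 33% | 52% | 39% | 61% |
| 35% | 21% v 14% | 7 points | 45% | 66% | 54% | 76% |

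If 50% v 30% still smoke instead, the result at s = 25% and n = 200 is 38% v 53%. Allowing 3% smoking among the others lowers whole-arm power further (33% to 29% at s = 25%, 60% v 40%, n = 200).

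**Step 4: size needed for 80% power, 60% v 40%.** Among smokers, 97 per arm. At s = 25% that is 97/0.25 = 388 evaluable patients per arm, against 686 per arm for the whole-arm comparison.

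**The case against.** The whole-arm rate is a valid randomised intention-to-treat contrast. It introduces no bias, and it answers a population question that suits an unselected, population-based cohort. It also counts relapse: ex-smokers can start again over 36 months, and the calls cover tobacco without being limited to current smokers. A reader might infer that only baseline smokers can change, or that the others carry no information. The article does not support that, and it is why the whole-arm rate should stay as a reported outcome.

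Statistical Methods already foresees baseline adjustment in exploratory analyses, and since all secondary outcomes are exploratory such an analysis would not rank far below the main one. But no covariate is named, so admission smoking status is not secured, and the outcome definition and the 10% benchmark stay as they are.

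The gain is also limited: restriction improves power without reaching 80% in any scenario above. And the 10-point benchmark is not arithmetically impossible, since 20% v 10% needs 199 per arm. Both points stand.

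A reader might extend the point to HbA1c and say it is compared in everyone tested. The article shows only that the test is part of the routine in both arms. Diabetes control most naturally refers to patients with diabetes, and no section states that the analysis covers everyone. At most an analysis set is left unspecified, which a condensed article may leave to the full protocol or analysis plan.

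**Conclusion.** The concern holds as one of efficiency and interpretation, and it is minor. Under the stated assumptions, analysing patients who smoked at admission raises power by about 13 to 21 percentage points at 200 evaluable per arm (21 to 34%, 33 to 52%, 45 to 66%). The 10-point benchmark corresponds to a gap among smokers of 29 to 67 points. The direction is the same at every smoker share tried; the size rests wholly on assumed prevalence and stopping rates, because the article gives none. It would be wrong to conclude that the planned comparison is biased or that the change makes the smoking analysis adequately powered. The primary LDL analysis is untouched.

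**What to change.** - In Outcomes and Statistical Methods, make the main smoking analysis the proportion not smoking at 12, 24 and 36 months among patients who smoked at the index admission, with the same logistic model. Alternatively, include admission smoking status as a named covariate in the whole-arm model.
- Keep the whole-arm smoking rate as a reported outcome, so that relapse and uptake are still captured.
- In Sample Size, give the control rate assumed behind the 10%, or restate the benchmark as a difference among admission smokers.
- Do not define the subset by smoking status at the 1-month contact. Patients are enrolled in hospital, so that status is self-reported after enrolment, and it would leave out patients who stopped at the event and may relapse.

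The cost is wording only; admission status precedes the intervention, so the randomised comparison is kept. The downsides are a smaller analysis set, power still below 80% in these scenarios, and reliance on smoking status at admission having been recorded, which is an assumption to check first.
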